**Methods and analysis:**

A parallel-group RCT with a mixed methods process evaluation as well as a cost-effectiveness evaluation will be conducted. We aim to recruit 240 PwMS, who will be stratified by ambulation level and randomised 1:1 in blocks of eight to intervention or control. The group-based self-management fall prevention intervention involves eight 2-hour online synchronous sessions (approximately eight participants/group) facilitated by a licensed healthcare professional and home assignments to be completed by participants between sessions. The setting is online, and participants can be located anywhere in Sweden. The control and intervention groups will also receive a brochure on fall risk factors and fall prevention in addition to their standard MS care and rehabilitation. Data collection will be performed at baseline and 3, 6 and 12 months after the start of the intervention. Falls will be monitored via a short message service every week during 1 year from the start of the intervention. The primary outcome is fall frequency (falls/person/year). Secondary outcomes include injurious falls, falls control, fear of falling, falls self-efficacy, activity curtailment, perceived effect of MS, self-rated health and cost-effectiveness.

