## Introduction

 Multiple sclerosis (MS) is a chronic inflammatory, demyelinating and neurodegenerative disease that typically is progressive in nature.^1^ Several symptoms of MS are known fall risk factors, including impaired balance, gait and cognition.^2 3^ In people with MS (PwMS), approximately 56% experience a fall within 3 months.^4^ Those PwMS who have experienced a fall in the past year have an 82% probability of falling again within 6 months and a 56% probability of an injurious fall.^5^ Falls among PwMS are associated with fear of falling, low health-related quality of life and injuries.^3 6^ Because PwMS frequently experience injurious falls,^7^ the socioeconomic costs for both PwMS and society are potentially high. Surprisingly, there are no studies on costs related to falls in PwMS. However, existing research describing the cost of falls for other patient populations with neurological problems ^8 9^ have suggested the high healthcare costs associated with falls among PwMS.

Despite the recognition that several MS symptoms influences fall risk,^2 3^ most fall prevention interventions for PwMS only address physical impairments. There is a major gap in existing evidence regarding behavioral and environmental influences on fall risk in PwMS. The importance of comprehensive approaches to fall prevention targeting modifiable risk factors through fall prevention programmes for PwMS has been highlighted.^10^ Another major gap in MS falls research is the scarcity of studies that focus on falls among the 25% of the MS population who can walk only a few steps or not at all, ie, are non-ambulatory.^6^ Fall prevention interventions for non-ambulatory PwMS show promising results but are rare.^11 12^ Although ambulatory and non-ambulatory PwMS share the same fall risk factors,^2 13^ new evidence suggests that some fall risk factors are unique to non-ambulatory PwMS.^13^ Thus, fall prevention programmes for PwMS must target the unique needs and multifactorial fall risks of PwMS, with consideration that members of the target audience may be ambulatory or non-ambulatory and typically will experience fluctuations in functional status and disease over time.

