### Recruitment and procedures

Participants will be recruited via flyers placed in inpatient and outpatient MS and rehabilitation clinics, from social media advertisements published by Karolinska Institutet, and by the patient organisation Neuro Sweden.

The notices will include a link to a webpage with study information and an online template where interested individuals can fill in their contact information. A research assistant with training in Good Clinical Practice^30^ will screen the completed templates regularly, contact potential participants by phone or e-mail (depending on PwMS’ choice of contact), and provide potential participants with information about the study. Individuals expressing interest in the study will be screened for eligibility. The informed consent process will be initiated with PwMS who meet the eligibility criteria. Specifically, eligible PwMS will be sent written information. Informed consent (online supplemental material) is obtained through BASS, an integrated online treatment and assessment platform. The platform is provided by the eHealth Core Facility at Karolinska Institutet, Stockholm, Sweden. Individuals providing informed consent will be included.

Baseline assessment will be supported by the use of the BASS database. The PwMS will subsequently be randomised to the intervention group or the control group using a data-generated system (Sealed Envelope Ltd. 2021). Participants will be stratified as non-ambulatory (able to walk a maximum of 5 m with assistance or not able at all) or ambulatory in a 1:1 allocation ratio of blocks of eight. Participants will be contacted by phone to inform them about group allocation.

Recruitment began in December 2023, and the expected completion of the study is January 2027. An overview of the study schedule of enrolment, allocation, intervention and assessments are presented in figure 1.

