### Analysis

#### Data management and statistical methods

##### RQ 1a, RQ 1b and RQ 2: effectiveness study

Intention-to-treat and per-protocol analyses will be performed. Per-protocol analyses will include participants who fulfil content adherence, defined as completion of at least two action plans.

Descriptive statistics will be used to present data, for example, means, medians, frequencies, SD, quartiles and counts. Drop-out analyses of baseline characteristics will be explored with parametric and non-parametric analyses depending on the data level.

The primary analysis for falls (falls/person/year) will be conducted using generalised linear mixed models (GLMM) with a Poisson link function to account for count data distribution and potential overdispersion. The model will include fixed effects for the intervention group and random effects for participant variations over time. Interactions between variables will be included if deemed necessary. Linear mixed model analyses will be used for normally distributed secondary outcomes. For categorical outcomes, GLMM with logistic or ordinal regression will be used, depending on the nature of the outcome (binary or ordinal). The primary endpoint is 6 months after the start of the intervention. In addition, analyses of sustainability of potential effects will be performed after 12 months. Any missing data will be handled using appropriate methods, such as multiple imputation, to ensure robustness in analyses. Analyses will be performed and reported in accordance with the Consolidated Standards of Reporting Trials (CONSORT) guidelines for RCT.^50^ A data management plan is established and stored at the Research Data Office at Karolinska Institutet.

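### Randomisation is stratified by ambulation, but the stated primary falls model names no ambulation term; if ambulation predicts falls, precision and power are given away

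*Protocol article*

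**What the plan says.** The Abstract (Methods and analysis) describes participants "who will be stratified by ambulation level and randomised 1:1 in blocks of eight to intervention or control". Recruitment and procedures repeats this and defines the strata: "Participants will be stratified as non-ambulatory" (5 m of assisted walking at most, or none) "or ambulatory in a 1:1 allocation ratio of blocks of eight".

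The Analysis section for RQ 1a, RQ 1b and RQ 2 specifies a Poisson generalised linear mixed model for falls: "The model will include fixed effects for the intervention group", together with random effects for how participants vary over time. It continues: "Interactions between variables will be included if deemed necessary". No part of the article names ambulation, or any other covariate, as a main effect in this model.

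**The concern.** Ambulation is the only stratification factor, and stratified blocks hold the arms close to balance on it. Differences in fall rate between ambulatory and non-ambulatory people therefore contribute almost nothing to the chance difference between arms. A model that does not know the stratum cannot see this. It puts the between-stratum spread into the participant random effect and charges it to the standard error of the rate ratio.

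What is at stake is precision: a confidence interval wider than the design requires, and less power at the 6-month primary endpoint. The error is on the conservative side.

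The article gives some reason to expect ambulation to matter. The Introduction says that "new evidence suggests that some fall risk factors are unique to non-ambulatory PwMS", and the investigators chose this factor to stratify on.

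**Working it through.** **Inputs from the article.** Pilot means of 2.45 (intervention) and 3.69 (control) falls in 18 weeks; 84 per group; power 0.8; alpha 0.05 (taken as two-sided); blocks of eight within stratum. The Introduction puts 25% of the MS population as non-ambulatory.

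**Assumptions.** The trial's non-ambulatory share is p = 0.25. The ratio R of the non-ambulatory to the ambulatory fall rate is not in the article, so it is varied.

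**The article's own figure.** The log rate ratio is ln(2.45/3.69) = −0.410, a rate ratio of 0.664. A plain Poisson calculation gives n = (1.960 + 0.842)² × (1/2.45 + 1/3.69) / 0.410² ≈ 32 per group, not 84. To have a realistic variance, I took the negative binomial dispersion k that makes 84 per group give 80% power without a stratum term:

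- V = 1/2.45 + 1/3.69 + 2k, and k = 0.558 gives V = 1.795.
- SE = √(1.795/84) = 0.146.
- Power = Φ(0.410/0.146 − 1.96) = 80%.

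**Effect of the stratum term.** The squared coefficient of variation between strata is B = p(1−p)(R−1)² / (1−p+pR)². With stratified allocation and the stratum in the model, V becomes V − 2B. For R = 2: B = 0.1875/1.5625 = 0.120, V − 2B = 1.555, SE = 0.136, power = Φ(0.410/0.136 − 1.96) = 85.3%.

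| R | B | V − 2B | SE with stratum | SE without / with | Power with stratum |
|---|---|---|---|---|---|
| 1 | 0 | 1.795 | 0.146 | 1.00 | 80.0% |
| 1.25 | 0.010 | 1.774 | 0.145 | 1.01 | 80.5% |
| 1.5 | 0.037 | 1.721 | 0.143 | 1.02 | 81.6% |
| 2 | 0.120 | 1.555 | 0.136 | 1.07 | 85.3% |
| 3 | 0.333 | 1.128 | 0.116 | 1.26 | 94.2% |

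Setting these powers against a fixed 80% overstates the gain at large R. The model without the stratum reports SE 0.146, but its estimate really varies with SE 0.116 at R = 3. Its power is then Φ((0.410 − 1.96 × 0.146)/0.116) ≈ 86%, a gap of about 9 points rather than 14. At R = 2 the same step gives about 82%, a gap of about 4.

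**Simulation.** Trials of 168 participants were simulated with blocks of eight within stratum, 25% non-ambulatory and a rate ratio of 0.664. Negative binomial fits stood in for the Poisson mixed model.

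| Set-up | R | Power without stratum | Power with stratum |
|---|---|---|---|
| Total dispersion 0.56 | 1 | 81.2% | 81.1% |
| | 1.5 | 81.0% | 82.2% |
| | 2 | 83.8% | 87.8% |
| | 3 | 89.2% | 95.3% |
| | 0.5 | 80.7% | 82.7% |
| Within-stratum dispersion 0.56 | 3 | 72.3% | 82.3% |
| | 0.5 | 82.3% | 84.7% |

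A further run (500 replicates, dispersion 0.56) gave no gain at R = 1 or 1.5, 3 to 4 points at R = 2 and about 8 at R = 3 (SE 0.164 without the stratum, 0.144 with it).

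**False positives without the stratum.** At R = 2, two runs of 1,500 replicates gave 3.9% and 4.9%. At R = 3 they gave 1.7% and 3.7%. The 500-replicate run showed no clear fall. The Monte Carlo margin around 5% with 1,500 replicates is 1.96 × √(0.05 × 0.95/1500) = 1.1 points.

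**The case against.** **The article does not say that arm is the sole fixed effect.** The sentence also omits time, although it refers to variation over time and allows interactions, and an unseen analysis plan may list covariates. This stands in part: the plan may already hold the term. But the article does set out the model's fixed and random effects, and the one factor used to stratify is not among them. Optional interactions do not prespecify a main effect.

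**A reader might infer that the standard error is in fact too wide and that power is certainly lost.** The article does not support this. It reports no fall rates by stratum, and the Introduction sentence that mentions unique risk factors also says that the two groups share risk factors. Unique risk factors do not establish different fall rates. For ratios up to 1.5 the loss is negligible. The 25% is a population share: eligibility requires independent walking or transfer and a fall in the past year, which may lower the share and narrow the difference. At 10% non-ambulatory the formula gives 80.9% at R = 1.5 and 83.3% at R = 2, against 80%.

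**A reader might also infer that the test rejects clearly below 5%.** At twofold this is not established, since the simulated rates lie within or at the edge of Monte Carlo error. At threefold the runs do not agree on how far the rate falls.

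**A reader might extend the remedy to every secondary outcome.** That fails. Under Data collection and outcome measures, the Short Falls Efficacy Scale-International goes to ambulatory participants and the Spinal Cord Injury Falls Concern Scale to non-ambulatory participants, so a stratum effect cannot be estimated there. For pooled scales with baseline modelled as a repeated response, stable stratum differences largely cancel from the change contrast. No secondary outcome was simulated.

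**Conclusion.** The point holds as a conditional one. The design stratifies by ambulation and the stated primary model does not name it. If ambulation predicts falls, the omission widens the standard error and costs power, without bias and without excess false positives.

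With 25% non-ambulatory and dispersion about 0.56, the cost is roughly 0 to 2 power points for stratum rate ratios up to 1.5, about 3 to 5 at twofold and about 6 to 14 at threefold. The 14 comes from the approximation that holds unadjusted power at 80%; the simulations give 6 to 10. A twofold lower non-ambulatory rate costs a little less, about 2 to 3 points. With equal rates nothing material changes (81.2% and 81.1%).

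The direction is secure. The size rests on a stratum rate ratio, a non-ambulatory share and a dispersion that the article does not give. The case for the change is that it can help and costs almost nothing, not that a large loss has been shown.

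**What to change.** In the Analysis section for RQ 1a, RQ 1b and RQ 2, or in the analysis plan, add a fixed effect for the randomisation stratum (ambulatory or non-ambulatory, as entered at randomisation) to:

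- the 6-month primary falls model;
- the 12-month falls model;
- each secondary-outcome model that pools both strata.

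Leave it out of the models for the Short Falls Efficacy Scale-International (ambulatory only) and the Spinal Cord Injury Falls Concern Scale (non-ambulatory only).

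Use the value entered at randomisation, because the Introduction expects functional status to fluctuate and a later value could differ from the one that governed allocation.

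The cost is one phrase and one degree of freedom. The stratum is already recorded, so no new data are needed. Fix it before outcomes are analysed; the article expects completion in January 2027.

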### Aim and research questions

This study aims to evaluate the effectiveness of the self-management fall prevention programme *Fewer Falls* on falls in PwMS. The hypothesis is that the fall frequency in the *Fewer Falls* intervention group will be lower than that in the control group.

Research questions (RQs):

RQ 1a: Is there a difference in fall frequency between the intervention group and the control group 6 months (primary endpoint) after the start of the intervention?

RQ 1b: Is there a difference in the fall frequency between the intervention group and the control group 12 months (sustainability) after the start of the intervention?

RQ 2: Are there differences in secondary outcomes between the intervention group and the control group?

RQ 3: How do process evaluation components (context, implementation and mechanisms of impact) inform the interpretation of outcomes?

RQ 4: What is the cost-effectiveness of *Fewer Falls* 12 months after the start of the intervention?

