### Data collection and outcome measures

#### RQ 1a, RQ 1b and RQ 2: effectiveness study

Data will be collected using the digital platform BASS database. The data collection will be blinded as the participants receive a link to the BASS database, which provides them with access to the questionnaires that are completed online. Baseline data includes the sociodemographic information (ie, age, sex, civil status, work status and educational level); disease-related characteristics (ie, MS severity, time since diagnosis, symptoms, medications and other treatments, other diagnosis and aids); formal/informal care; cognitive function (collected through the short version of the Montreal Cognitive Assessment Scale^36^); anxiety and depression (collected through the Hospital Anxiety and Depression scale^37^); fatigue (assessed by the Fatigue Severity Scale^38^); health literacy (assessed via the Swedish version of the Health Literacy Survey European Questionnaire/16 item version^39^); self-reported falls and fall related injuries in the previous 6 months; and expectations on the programme.

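### The primary falls model names only the intervention group as a fixed effect, leaves interactions to a rule without criterion, and does not state the window of the 12-month sustainability analysis

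*Protocol article*

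**What the plan says.** The effectiveness part of the protocol article's section on data management and statistical methods chooses "generalised linear mixed models (GLMM) with a Poisson link function to account for count data distribution and potential overdispersion". It then gives the model's content: "The model will include fixed effects for the intervention group and random effects for participant variations over time". The next sentence reads "Interactions between variables will be included if deemed necessary". No covariate, time or period term is named.

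Under Recruitment and procedures, the randomisation uses one two-level factor: "Participants will be stratified as non-ambulatory (able to walk a maximum of 5 m with assistance or not able at all) or ambulatory". Groups are of equal planned size, with a block length of eight. Under Data collection and outcome measures, the baseline data include "self-reported falls and fall related injuries in the previous 6 months".

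RQ 1a places the primary endpoint at 6 months. RQ 1b asks about the group difference "12 months (sustainability) after the start of the intervention". The analysis section announces a further sustainability analysis after 12 months. It does not say whether that covers months 0-12 or only the second half-year, nor which model it uses.

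**The concern.** Three things in the stated model could be improved at almost no cost.

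- **Covariates.** The stratification factor and a baseline count of the outcome, over a window as long as the primary one, are both available. A model without them leaves explainable between-person variation in the error. At stake is precision, and hence power.
- **Interactions.** The rule sits in the paragraph that defines the primary analysis. It does not say which interactions, on what grounds, when or by whom. Once an interaction with group enters, the main group coefficient means something different, so the primary estimate is not fixed by the text.
- **Sustainability.** Falls are recorded weekly for 12 months. If the 12-month analysis takes all 12 months with only a group effect, it blends early and late effects and cannot separate an effect that lasted from one that faded.

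**Working it through.** **Inputs from the protocol article.** Pilot means over 18 weeks of 2.45 (intervention) and 3.69 (control); 84 per group; power 0.8; alpha 0.05 (taken as two-sided); 1:1 allocation; primary endpoint at 6 months.

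**Assumed inputs, not in the article.** Pilot rates constant out to 26 weeks; negative-binomial dispersion k of 1.14 or 0.66; correlation r of 0.3, 0.5 or 0.6 between baseline falls and follow-up log fall rate, reducing between-person variance by the factor 1 - r².

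**1. The plan's own figure.** Plain Poisson, log rate ratio: n = (1.960 + 0.842)² × (1/2.45 + 1/3.69) / ln(2.45/3.69)² = 7.849 × 0.6792 / 0.1677 = 31.8, so 32 per group. This does not reproduce 84. That is a separate matter; here it shows only that variance beyond Poisson has to be assumed. Over 26 weeks the means become 2.45 × 26/18 = 3.54 and 3.69 × 26/18 = 5.33. The k at which 84 per group gives 80% power is (84 × 0.1677/7.849 - (1/3.54 + 1/5.33))/2 = (1.795 - 0.470)/2 = 0.66. The value 1.14 serves as a more dispersed alternative.

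**2. Power with and without the baseline count.** Power = Φ(0.4095 / √(v/84) - 1.96), with v = 1/3.54 + 1/5.33 + 2k(1 - r²) = 0.470 + 2k(1 - r²).

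| r (assumed) | 1 - r² | v, k = 1.14 | power | v, k = 0.66 | power |
|---|---|---|---|---|---|
| 0 | 1.00 | 2.750 | 0.62 | 1.790 | 0.80 |
| 0.3 | 0.91 | 2.545 | 0.65 | 1.671 | 0.83 |
| 0.5 | 0.75 | 2.180 | 0.72 | 1.460 | 0.87 |
| 0.6 | 0.64 | 1.929 | 0.77 | 1.315 | 0.91 |

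**3. Validity check by simulation.** Settings: 168 participants, blocks of eight, about 24% non-ambulatory, stratum rate ratio 0.5 to 2, k about 0.66, half of the log-rate variance shared with baseline, 400 runs per scenario. Negative-binomial regression stood in for the mixed model. Every setting beyond the block size and total number is an assumption.

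- With no treatment effect, the group-only model rejected in 0.025 to 0.075 of runs. That is compatible with 0.05, given simulation error of about ±0.02.
- With the pilot effect, adding stratum and baseline count reduced the standard error of the log rate ratio from 0.135-0.143 to 0.128-0.129, about 5-10%. Power went from 0.81-0.86 to 0.86-0.89.

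**4. The 12-month window.** Suppose the pilot ratio 2.45/3.69 = 0.664 holds in months 0-6 and 1.00 in months 7-12, with equal control rates in both halves. A group-only model over 12 months then targets (0.664 + 1.00)/2 = 0.83. The pattern is hypothetical and shows only what the choice of window can hide.

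**The case against.** The strongest reply is that this is a condensed article. It says what the model will include and excludes nothing, and a covariate list commonly belongs in an analysis plan that is not shown. That stands. A reader might infer that the trial has decided to ignore the stratum and the baseline count; the text supports only that group is the one fixed effect named.

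Four further points also stand.

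- A reader might infer bias or an invalid test from leaving out the stratum. In a randomised comparison the cost is precision, and the simulated type I error gives no sign of inflation.
- A reader might infer that interactions will be picked after the results are seen. The article does not say when or by whom necessity is judged; it merely fails to rule this out.
- A reader might infer that RQ 1b cannot be answered without a group-by-period term. It can: a separate model restricted to months 7-12 would do, and the article announces a separate 12-month analysis without giving its form.
- Baseline falls are recalled over 6 months, whereas follow-up falls come from weekly text messages. The correlation could therefore lie at the low end, where the gain is small.

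The reply does not reach the interaction sentence. That is written text, not an omission, and it leaves the primary model open.

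**Conclusion.** The concern holds as a matter of efficiency and pre-specification. It is not a challenge to the validity of the trial. The interaction rule is the firmest part, since it rests on the wording alone.

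The precision argument is sound in direction, but its size depends on a k and a correlation that the article does not give. The illustrated gain runs from about 0.03 in power (r = 0.3, either k) to about 0.15 (r = 0.6, k = 1.14). It also assumes that the pilot's 18-week rates carry over to 26 weeks.

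On RQ 1b, what can be said is that the window is not stated. The value of 0.83 illustrates what pooling over 12 months could conceal; it does not predict what the trial will do.

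**What to change.** 1. Name ambulation stratum and the baseline 6-month fall count, for example as log(count + 1), as fixed effects beside group in the primary model.
2. For RQ 1b, state the window and pre-specify the months 7-12 rate ratio as the sustainability result, from either a group-by-period term or a separate model for those months.
3. Remove the interaction rule from the confirmatory analyses and label any other interactions exploratory.

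This is a change of wording; both covariates are already collected. It costs a few degrees of freedom, and the months 7-12 estimate will be less precise than one pooled over 12 months. Recruitment began in December 2023 and completion is expected in January 2027, so the change should be dated and made before outcome data are examined by group. If an analysis plan already fixes these points, the article's sentence need only be aligned with it.
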